## Abstract

**Background:**

Hospitals are frequently faced with high levels of emergency department presentations and demand for inpatient care. An important contributing factor is the subset of patients with complex chronic diseases who have frequent and preventable exacerbations of their chronic diseases. Evidence suggests that some of these hospital readmissions can be prevented with appropriate transitional care. Whilst there is a growing body of evidence for transitional care processes in urban, non-indigenous settings, there is a paucity of information regarding rural and remote settings and, specifically, the indigenous context.

**Methods:**

This randomised control trial compares a tailored, multidimensional transitional care package to usual care. The objective is to evaluate the efficacy of the transitional care package for Indigenous and non-Indigenous Australian patients with chronic diseases at risk of recurrent readmission with the aim of reducing readmission rates and improving transition to primary care in a remote setting. Patients will be recruited from medical and surgical admissions to Alice Springs Hospital and will be followed for 12 months. The primary outcome measure will be number of admissions to hospital with secondary outcomes including number of emergency department presentations, number of ICU admissions, days alive and out of hospital, time to primary care review post discharge and cost-effectiveness.

**Discussion:**

Successful transition from hospital to home is important for patients with complex chronic diseases. Evidence suggests that a coordinated transitional care plan can result in a reduction in length of hospital stay and readmission rates for adults with complex medical needs. This will be the first study to evaluate a tailored multidimensional transitional care intervention to prevent readmission in Indigenous and non-Indigenous Australian residents of remote Australia who are frequently admitted to hospital. If demonstrated to be effective it will have implications for the care and management of Indigenous Australians throughout regional and remote Australia and in other remote, culturally and linguistically diverse populations and settings.

**Trial registration:**

Australian New Zealand Clinical Trials Registry, ACTRN12615000808549- Retrospectively registered on 4/8/15.

**Electronic supplementary material:**

The online version of this article (doi:10.1186/s12913-017-2077-7) contains supplementary material, which is available to authorized users.

## Background

### The impact of frequent hospital attendance on patients and hospitals

Hospitals are frequently faced with high levels of emergency department presentations and demand for inpatient care. These demands often exceed the available resources especially in regional and remote areas where alternate hospitals or services are distant and difficult to access. Delayed emergency department review, admitted patients waiting in emergency departments and long hospital elective waiting lists can, in part, be traced back to a lack of inpatient beds [1–4]. An important contributing factor to this mismatch between the demand for inpatient care and its availability is the admission of an often small but important sub-set of patients who have frequent and preventable exacerbations of their chronic diseases [5]. This is often compounded by a lack of, or limited access to, community-based social and primary health care supports. Such hospital admissions remove an individual from their family and community supports, limit their ability to undertake usual activities and expose them to risk of infection and other nosocomial complications. Many of these are patients with chronic and other diseases that can, with appropriate community-based management and support, avoid de-compensation and the need for inpatient care [6–8].

Recurrent readmissions also pose a financial burden on a health system that is faced with escalating costs. In the US, nearly half of the total health care budget is spent on inpatient services. Existing studies have demonstrated that readmissions account for one quarter of total inpatient expenditure [9, 10]. Given its impact on total health care expenditure cost containment associated with acute inpatient care is an important focus [11]. This has encouraged the development of initiatives that aim to decrease length of inpatient stay, increase the use of day procedures, transfer care to the community setting including “hospital in the home” programs and reduce preventable hospital readmission [10, 12]. Evidence indicates that even a small reduction in readmission numbers could have a substantial financial benefit.

### Preventing repeated attendance and readmission to hospital

Existing literature suggests many hospital readmissions are related to preventable or avoidable causes [13]. Targets for initiatives that might reduce readmission include improved patient and family education and community-based support, pre-discharge planning and community and primary health care based liaison, early follow-up and ongoing chronic disease management. Despite many health care services allocating significant resources to facilitating hospital discharge and preventing readmission evidence supporting a particular approach is limited and largely lacking for disadvantaged, remote and Indigenous Australian populations.

One hospital-based readmission prevention initiative is discharge planning. This involves the development of an individualised plan for a patient prior to leaving hospital. The aim is to reduce length of hospital stay and unplanned readmission, and improve the coordination of hospital and community-based services following discharge [14]. Evidence suggests that a coordinated discharge plan tailored to the individual patient brings about a reduction in length of hospital stay and readmission rates for adults with complex medical needs. Specific interventions include formal assessment for risk factors relating to delayed and failed discharge, patient education, medication reconciliation, discharge care plans and post discharge follow-up including telephonic review, home visits and timely review with a primary care provider. Dedicated discharge planning staff to coordinate this process has been highlighted as an important contributor to the success of such programs [15, 16].

Many hospitals are already making a significant investment in attempting to reduce inpatient stays and readmission in the form of designated discharge planning positions and allied health, pharmacy, drug and alcohol, social work, mental health, aged, rehabilitation and palliative care services. While such services are variably available and accessed by all Australians, the need is even greater for remote residents, who already face limited access to health care, and Indigenous Australian patients who are more likely to face issues relating to a greater burden of co-morbidity, language, intercultural communication, remoteness and economic and environmental disadvantage.

### Alice Springs Hospital and frequent hospital admissions

Alice Springs Hospital is the regional referral centre for Central Australia. It has a catchment of approximately 50,000 residents incorporating Alice Springs and up to 50 remote communities that range between 80 and 1000 kms from the hospital. Indigenous Australians, who are often faced with significant and complex health needs, represent 40% of this population. A combination of a remote population with a high burden of complex and chronic disease can result in high levels of emergency patient presentations to Alice Springs Hospital and delays in transfer to inpatient wards which can in turn rapidly lead to an overcrowded emergency department, increased waiting times and, by extension, poorer patient outcomes [3]. As previously noted, an important potential factor contributing to this issue are patients who repeatedly attend hospital and require admission due to a combination of preventable exacerbations of their chronic disease and a lack of community-based support.

A particular group at risk of re-admission to Alice Springs Hospital are adult patients with, usually multiple, chronic but not immediately life threatening diseases such as chronic lung (Chronic Obstructive Pulmonary Disease (COPD)/bronchiectasis/asthma) and heart (heart failure, coronary artery disease) disease [17, 18]. In Alice Springs, many of these patients are Aboriginal people who may live in Alice Springs or remote communities up to 1000km distant from the hospital. In 2012, excluding oncology and renal dialysis patients, there were more than 320 adult medical patients (90% Aboriginal Australian) admitted to Alice Springs Hospital who had more than five admissions over the preceding year. These patients had an average of eight admissions per year and accounted for over 2500 admissions or approximately 25% of adult medical admissions. Thus, 320 adult medical patients or less than 1% of the adult population of Central Australia, accounted for one quarter of the admissions to the adult medical service at Alice Springs Hospital.

There is currently no consistent definition for unplanned hospital readmissions. This makes comparison of data difficult and as a result readmission data is not part of current hospital performance frameworks. Australian data indicate that across all hospitals (public and private) and age groups, 1% of patients are readmitted within 28-days [19]. A recent study at Flinders Medical Centre in South Australia found that just over 10% of patients were being readmitted within 28 days of discharge. Those patients with respiratory, neurological or genitourinary and trauma were more likely to be readmitted. Risk factors for readmission included increased length of stay, high co-morbidity index scores and discharge against medical advice [19].

Much of the current research relating to miminising hospital stay and readmission has been conducted with specific medical populations including heart failure or COPD [20–25]. Recent data from three randomised trials indicated that multidisciplinary home-based case management for patients hospitalised with the full spectrum of chronic heart disease are effective in prolonging days alive and out of hospital and avoiding recurrent hospitalisation [26]. Whilst some research has been conducted in vulnerable populations, including low socioeconomic or ethnic minority groups [27–29], such studies do not specifically address the unique aspects of discharge planning when dealing with vulnerable, remote populations with a high burden of disease. There are few specific Australian studies especially those dealing with a rural/remote context.

Given the lack of evidence, we aim to extend and adapt the principles of what are often disease-specific, non-Indigenous and urban based models of readmission prevention and to evaluate such a more generic model linking hospitals with primary health care and other community-based resources in a remote setting with a large Aboriginal Australian population. To achieve this we aim to evaluate the efficacy of a tailored multi-dimensional case-based intervention for people with frequent admissions to the adult specialist medical and surgical service of a remote Australian hospital with a particular focus on the needs of Aboriginal people.

## Hypothesis

Relative to standard management, a targeted case management and discharge planning process aimed at adult medical and surgical inpatients with a history of a) four or more admissions over the last 12 months or b) more than seven admissions over the previous 24 months will be effective in reducing the rate of all-cause rehospitalisation (primary endpoint) and health care utilisation in the 12 months following the index admission.

## Methods/Design

### Objectives

The primary objective of this study is to compare a tailored discharge planning and case management approach for patients who are frequently admitted to Alice Springs Hospital with patients receiving usual care using the primary outcome of decreased readmissions. To do this we will:i.Develop and evaluate a multidimensional discharge planning and case-management approach aimed at reducing all-cause readmissionsii.Identify factors which predict readmission and subsequent mortality and thus factors which identify patients who are most likely to benefit from this interventioniii.Evaluate the efficacy and cost-effectiveness of this tailored case management-based approach

### Study design

In this randomised control trial conducted according to CONSORT guidelines for a pragmatic trial of a health service intervention, participants will be randomly allocated to either of two study arms using a concealed allocation procedure [30]. The study arms will include an intervention group who will participate in the case management approach over 12 months and a control group who will receive usual hospital-based care including discharge planning using the existing hospital-based, nurse led service. The case management approach will be delivered by a team consisting of a medical officer, Aboriginal Health Practitioner, nurse and pharmacist. Figure 1 summarises a patient’s journey through the study protocol.

**Fig. 1 Fig1:**
[figure not shown]
Patient flow through study protocol

Data collection will occur at enrolment, at each subsequent admission to hospital and at the conclusion of the study when primary health care utilisation and survival data will be collected. The primary outcome of interest will be a reduction in the number of admissions to hospital over the 12 month period following enrolment and will be based on intention to treat.

### Study setting

This study will be conducted at Alice Springs Hospital, the regional referral centre for remote Central Australia with 186 inpatient beds. It is the major teaching hospital servicing approximately 50,000 residents of both Alice Springs and up to 50 remote communities that range between 80 and 1000kms from the hospital (See Fig. 2). The nearest tertiary hospital referral centres, Darwin and Adelaide, are approximately 1500 km away by road.

**Fig. 2 Fig2:**
[figure not shown]
Map of catchment area for Alice Springs Hospital

### Study population

Subjects will be identified within 48 h of admission under an adult, general medical or surgical team. Alice Springs Hospital does not have sub-specialty adult medical units (e.g. cardiology, gastroenterology etc.) but each of the three adult general medical units tend to focus on one or more medical sub-specialties. Surgical patients will be required to have one or more pre-existing chronic disease diagnoses which have contributed to the current admission (e.g. foot ulcer with diabetes). Whilst enrolment will not be restricted to Indigenous Australians the majority of people requiring frequent admission to Alice Springs Hospital are Aboriginal Australians.

### Inclusion criteria

18 years and older4 or more adult medical and/or non-elective surgical admissions over the preceding 12 months or 8 over the preceding 24 monthsSurgical admissions will be counted if deemed a consequence of a chronic disease such as diabetic foot infections, acute/chronic pancreatitis and cellulitis
Resident of Central Australia (including the cross border regions of Western Australia and South Australia and extending north to Elliot in the Northern Territory).

### Exclusion criteria

Anticipated life expectancy of 12 months or less based on treating specialist assessmentStage 5 chronic kidney disease (eGFR < 15ml/min or receiving renal replacement therapy)Solid organ transplant (including renal transplant)Active palliative care involvementPreviously been enrolled in the study (such subjects will have on-going care as per their original study allocation)

### Randomisation: allocation, concealment and sequence generation

A computerised randomisation database using Microsoft Access will be utilised. Given the resource implications of the intervention, the randomisation ratio will be unequal with one participant allocated to the intervention group for every two allocated to the control group. Block randomisation will be used to randomly assign participants to intervention or usual care with participants being randomised in blocks of 21. Each block will have seven participants randomly assigned to the intervention and 14 participants to the control arm. Once eligibility is confirmed and the participant consented, the local study team will enter the enrolled participant’s details into the database and allocation will be automatically assigned.

Whilst allocation will be concealed the nature of the intervention will mean participants, research team member and local health care staff are aware of which group each participant has been allocated to. Staff assessing primary endpoint data and those involved with the analysis will be blinded to the study allocation.

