### Recruitment strategies and consent

Participants will be actively recruited through Alice Springs Hospital over a 24 month period. A list of new admissions to any of the adult general medical teams will be assessed daily for patients who meet admission criteria. Twelve month prognosis will be specifically assessed by asking the treating specialist physician whether they anticipate a potential participant will be alive in 12 months. If the treating clinician believes the patient will be alive, or is unsure whether this is likely, they will be deemed as potentially eligible. Such patients will be assessed against inclusion/exclusion criteria and, if eligible, will be approached by staff to invite them to take part in the study. We have ethics approval to follow-up patients deemed to have a prognosis less than 12 months at the end of the trial with no additional consent required (HREC-13-159).

The consent process will include explaining the details of the study with particular reference to the study design, the possibility participants will be allocated to a control/usual care group, the nature of the intervention and the confirmation that refusal or later withdrawal will not have implications for ongoing health care. The participant consent and information forms can be found in Additional files 1 and 2. Where appropriate the Aboriginal Health Practitioner member of the research team will facilitate these discussions to ensure comprehension and cultural security for Indigenous Australian patients. If necessary local Aboriginal language translators conversant in Central Australian languages (including Arrernte, Warlpiri, Yankunytjatjara, Pitjantjatjara, Luritja, Pintupi-Luritja, Ngaatjatjarra, Ngaanyatjarra, Alyawarra and Anmatyerre) and local English idioms will be used if standard English comprehension is limited [36]. A written English language information sheet will also be provided and consent to participate confirmed with a signed and witnessed consent form.

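### One constant block size of 21 in a single-site, open-label trial leaves up to about one allocation in ten predictable to a recruiter who knows the size and keeps count

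*Protocol article*

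**What the plan says.** The Randomisation section of the Protocol article sets the ratio: "the randomisation ratio will be unequal with one participant allocated to the intervention group for every two allocated to the control group". It then sets the scheme: "Block randomisation will be used to randomly assign participants to intervention or usual care with participants being randomised in blocks of 21", and "Each block will have seven participants randomly assigned to the intervention and 14 participants to the control arm". It gives no second block size and no stratification factor. Study setting gives a single hospital: "This study will be conducted at Alice Springs Hospital, the regional referral centre for remote Central Australia with 186 inpatient beds".

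On concealment, Study design states that "participants will be randomly allocated to either of two study arms using a concealed allocation procedure". The Randomisation section describes how this works: after eligibility is confirmed and consent given, "the local study team will enter the enrolled participant’s details into the database and allocation will be automatically assigned". It also says that, because of the nature of the intervention, "participants, research team member and local health care staff are aware of which group each participant has been allocated to". Only the staff assessing primary endpoint data and those involved in the analysis are blinded.

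Under Recruitment strategies and consent, new admissions are assessed daily and eligible patients "will be approached by staff to invite them to take part in the study". The Aboriginal Health Practitioner on the research team helps with consent discussions where appropriate. The 12-month prognosis is judged by the treating specialist, and an unsure answer leaves the patient potentially eligible.

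**The concern.** Once all seven intervention places in a block are used, every remaining place is control. Once all 14 control places are used, every remaining place is intervention. In an open-label trial with one sequence and one constant block size, past allocations are enough to work this out for anyone who knows the size. Automatic assignment after consent does not prevent it, because the decision whom to approach, and when, comes before the database is opened.

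This trial has some exposure. The people who know past allocations overlap with those who recruit. Eligible patients return often: Sample size gives a mean of eight admissions a year. The exclusion criteria bar only those already enrolled, so a patient who is not approached today can still be enrolled later. If staff held back certain kinds of patient when the next place was known, the arms would differ at baseline in ways that adjustment could correct only for measured factors.

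**Working it through.** The document gives no figure for predictability, so there is none to reproduce.

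**Inputs.** Block of 21 with 7 intervention and 14 control (Randomisation section). Total 210, as 70 and 140, hence 210/21 = 10 whole blocks; mean eight admissions a year, SD 4, planned reduction 25%, so a difference of 2.0 (Sample size). Recruitment over 24 months (Recruitment strategies and consent).

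**Step 1: places known with certainty to a perfect counter.** For a block with *a* intervention and *b* control places:
- expected controls left when intervention places run out: b/(a+1) = 14/8 = 1.75
- expected intervention places left when controls run out: a/(b+1) = 7/15 = 0.467
- total 2.217 per block; 2.217/21 = 10.6%; over 10 blocks, about 22 of 210.

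A simulation of 200,000 blocks gave 2.216.

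**Step 2: length of the known run at the end of a block.** The last place is always known.
- At least the last two known: [C(14,2) + C(7,2)]/C(21,2) = (91 + 21)/210 = 53%.
- At least the last three known: [C(14,3) + C(7,3)]/C(21,3) = (364 + 35)/1330 = 30%.

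**Step 3: guessing over all places.** Always guessing the arm with more places left in the block, computed by exact recursion, is right 70.0% of the time. Always guessing control is right 14/21 = 66.7% of the time. The gain is 3.3 percentage points.

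**Step 4: worst-case bias, an illustration on assumptions.** Assume half of patients are high-need, that high- and low-need patients differ by 4 admissions a year, and that every known intervention place is given to a high-need patient and every known control place to a low-need one.
- Intervention arm: share of high-need patients rises by 0.5 × 0.467/7 = 0.033.
- Control arm: share falls by 0.5 × 1.75/14 = 0.0625.
- Shift in the arm difference: 4 × (0.0333 + 0.0625) = 0.38 admissions a year (a simulation of ten-block trials gave 0.39), about 19% of 2.0.
- Steering half the time halves this to 0.19.

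The shift adds admissions to the intervention arm, so it works against the intervention. With SE = 4 × √(1/140 + 1/70) = 0.586, two-sided power at a difference of 2.0 is 93%. At 2.0 − 0.38 = 1.62 it is 79%.

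**Step 5: timing.** 210/24 = 8.75 enrolments a month, so a run of 2.2 known places lasts about 8 days. Eight admissions a year is one every 52/8 = 6.5 weeks.

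**Step 6: alternatives.** Sizes are drawn at random and the observer knows the set of sizes but not the draws.

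| Scheme | Certain places | Best-guess success |
|---|---|---|
| Constant 21 | 10.6% | 70.0% |
| Random 15, 18, 21, 24 | about 0.6% | 68.6% |
| Random 6, 9, 12 | about 2.1% | 71.8% |

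Varying the size removes most of the certainty. Choosing small sizes gives some of that back as better guessing, so the sizes should stay large.

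**The case against.** The strongest reply is that nothing shows anyone could or did use this. The article does not say that recruiters are told the block size or keep a tally, and whether the size was masked is a detail that an article commonly leaves to the full protocol. The next assignment cannot be looked up before consent. Twenty-one is a large block, the average gain in guessing is small, and known intervention places number only about five in the whole trial (0.467 × 10). Screening is daily, the admission-count criteria are numerical, and the prognosis call belongs to the treating specialist. A patient passed over during a known control run would usually return after it has ended, but to a chance of intervention near one third.

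Most of this stands. It makes 10.6% a ceiling and limits the importance of the point. It does not remove it: average guessing accuracy understates the exposure, because selection would work through the places that are certain, and consecutive approach is a written procedure that the allocation scheme does nothing to protect.

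A reader might infer more: that allocation is not concealed, that recruiters know one allocation in ten, or that the recruiting team made or holds the list. The documents support none of these. Predictability is not access to the sequence, and the article does not say who generated it.

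**Conclusion.** The constant block size is a modest, avoidable weakness. Up to 10.6% of allocations (about 22 of 210) could be known in advance, on two assumptions that the article neither states nor excludes: the recruiter knows the size, and keeps an exact count.

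This does not contradict the statement that allocation is concealed and is no sign of a breach. The direction of any bias is open. Steering high-need patients to the intervention would mask benefit, by at most about 0.38 to 0.39 admissions a year under the assumptions in the illustration; steering likely responders there would exaggerate it. The figure also assumes perfect recognition of high-need patients and steering at every known place, so it marks an extreme and is not an estimate. The change is worth making because it is cheap, not because harm has been shown.

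**What to change.** Replace the constant block of 21 with permuted blocks of randomly varying size in multiples of three, 1:2 within each block, for example 15, 18, 21 and 24. State that the sizes are withheld from recruiting staff. If recruitment is still open, apply this from the next block.

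If recruitment has closed, report the constant block size as a limitation and compare baseline characteristics, prior admissions in particular, by position within block.

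Cost: a new list loaded into the existing database. The ratio, total and power are essentially unchanged; the final arms may differ from 70 and 140 by a few participants if the last block is incomplete.
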